### Outcomes

The primary outcome is live birth rate per woman randomised, as defined previously [35].

Secondary outcomes include:ongoing pregnancy per woman randomised (defined as continuing pregnancy diagnosed by ultrasonographic visualisation of one or more gestational sacs on or after 12 weeks gestation)clinical pregnancy per women randomised (defined as a pregnancy diagnosed by ultrasonographic visualisation of one or more gestational sacs, including ectopic pregnancy)biochemical pregnancy (defined as βhcg > 25 mIU/ml) PIP-IVF onlymultiple pregnancies per women randomised and per clinical pregnancy (defined as ultrasonographic visualisation of two or more gestational sacs or heartbeats)ectopic pregnancy per women randomised and per clinical pregnancy (defined as a pregnancy in which implantation takes place outside the uterine cavity)miscarriage per women randomised and per clinical pregnancy (defined as the spontaneous loss of a clinical pregnancy before 20 completed weeks of gestational age)neonatal characteristics (for example, gender, gestation at birth, malformations)placenta characteristics (placenta previa: major, placenta previa: minor, placental abruption, placenta accreta: previous uterine surgery, placenta accreta: no previous uterine surgery)pain during the procedure (as measured by a 10 cm visual analogue scale (VAS))bleeding the day following the procedure.

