##### PIP-IVF

Planning to undergo autologous embryo transfer

Fertility clinics that routinely perform single embryo transfers are eligible to recruit for the PIP-IVF study. As per the pragmatic nature of the PIP studies, a number of women undergoing double embryo transfers will be recruited. The proportion of women in PIP-IVF who are undergoing double embryo transfers should not exceed the normal proportion of women who undergo double embryo transfers at the participating clinics (no more than 20 % [3]).

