### Statistical analysis

Demographic and baseline data will be compared between the two groups using the chi-squared test or *t*-test. Outcome data for the primary analyses will be treated in an intention-to-treat manner, such that all participants remain in the groups to which they were randomised. If no outcome data is available for the primary outcome of live birth, this will be imputed to assume that women with no outcome data did not have a live birth. Sensitivity analyses based on different assumptions may be used for secondary analyses. Per protocol analyses will be conducted as a secondary analysis.

For binary outcomes (for example, live birth), risk ratios will be calculated with associated 95 % confidence intervals and *p* values. ANOVA or logistic regression analysis will be used for the analysis of pre-specified subgroup effects. For continuous outcomes (such as pain), the mean difference will be calculated and the student’s *t*-test will be used.

Assessment of participant blinding will be performed using both James’ and Bang’s blinding indices [47, 48]. All statistical analysis will be performed using STATA or a similar statistical programme.

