#### ᅟ

##### PIP-UE

Type of embryo transfer (fresh or frozen)Number of embryos transferred (single or double)Number of previous embryo transfer procedures not resulting in a clinical pregnancy (for example, 0–1, 2–4, ≥5)Number of embryos transferred previously not resulting in a clinical pregnancy (for example, 0–1, 2–4, ≥5)Timing of endometrial biopsy (for example, follicular phase: cycle prior to embryo transfer cycle, luteal phase: cycle prior to ET cycle, follicular phase: embryo transfer cycle)Major cause of infertility (for example, male factor, endometriosis, ovulatory factor, unexplained, tubal factor, other)History of endometriosis (endometriosis or no endometriosis)Type of IVF (IVF or ICSI)Type of stimulation protocol (for example, long agonist, ultralong agonist, short agonist, antagonist)Duration of infertility (for example, < 2 years, 2–5 years, >5 years)Stage of embryos at transfer (for example, day 5/6 or day 2/3)

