##### PIP-UE

Presence of endometriosis (endometriosis or no endometriosis)Timing of endometrial injury (for example, during menstruation or not)Duration of infertility (for example, < 2 years, 2–5 years, >5 years)

For the outcome of pain during the procedure the following subgroup analysis will be performed:Previous cervical surgery (yes or no)Whether a tenaculum was used during the procedure (yes or no)Whether the procedure was performed during menstruation (yes or no).

Subgroup analyses will also be conducted to assess whether the probability of completing the endometrial biopsy procedure (that is, not abandoning the procedure) or needing a tenaculum to complete the procedure, is associated with the age of the woman or whether she had previous cervical surgery.

Any subgroup analyses conducted which are not pre-specified will be clearly stated as ad hoc and will be used for hypothesis generating only.

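### The live-birth risk ratio is planned without baseline covariates while baseline data are significance-tested between arms; pre-specified adjustment would give a modest gain in precision for a change of wording

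*Protocol article*

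**What the plan says.** - **Outcome.** "The primary outcome is live birth rate per woman randomised" (Outcomes).
- **Primary comparison.** "For binary outcomes (for example, live birth), risk ratios will be calculated with associated" 95% confidence intervals and p values (Statistical analysis). No covariate or stratification factor is named. The words crude and unadjusted do not appear.
- **Regression.** The same paragraph offers ANOVA as one option; as the other, "logistic regression analysis will be used for the analysis of pre-specified subgroup effects".
- **Baseline data.** "Demographic and baseline data will be compared between the two groups using the chi-squared test" or the t-test (Statistical analysis).
- **Prognostic variables used elsewhere.** The first list under Subgroup analyses is headed PIP-UE, but its items belong to IVF. It includes "Number of previous embryo transfer procedures not resulting in a clinical pregnancy" and duration of infertility. The PIP-PCOS list has previous ovulatory induction cycles, and the PIP-UE list proper has duration of infertility.
- **Female age.** Age is an eligibility limit in PIP-UE and PIP-PCOS. It also appears in the analysis of whether completing the procedure, or needing a tenaculum, "is associated with the age of the woman or whether she had previous cervical surgery". It is in no live-birth analysis.
- **PIP-IVF entry.** The only listed inclusion criterion is "Planning to undergo autologous embryo transfer", with no age limit.
- **Randomisation.** Allocation is 1:1, stratified by clinic and, in PIP-IVF, by fresh or frozen-thaw transfer.

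**The concern.** The trials admit women of varied prognosis by design, and in PIP-IVF without an age limit. Prognostic variation left out of the primary analysis widens the confidence interval of the risk ratio. The plan already needs several plausible predictors for other analyses, so using them in the primary model would be nearly free.

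The baseline tests add nothing in exchange. Under valid randomisation any baseline difference is due to chance, so the null hypothesis of each test is known to be true. About 1 test in 20 will fall below 0.05 whatever the quality of the trial. Such a result says nothing about whether the variable matters for live birth, which is what decides whether it should be adjusted for.

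At stake is some precision, mainly if the true effect is smaller than the design effect.

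**Working it through.** **1. The plan's sample sizes.** None of them assumes adjustment. For two proportions, two-sided 5%, 90% power, women per arm:

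| Trial | Rates | Pooled formula | With continuity correction | Stated |
|---|---|---|---|---|
| PIP-IVF | 33% v 17% | 152 | 165 | 188 |
| PIP-UE | 20% v 7% | 144 | 159 | 158 |
| PIP-PCOS | 32% v 14% over three cycles | 113 | 124 | 126 |

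The PIP-PCOS rates are 1 − 0.88³ = 31.9% and 1 − 0.95³ = 14.3%, rounded. The last two stated figures are reproduced closely with the continuity correction. The PIP-IVF figure of 188 is what the pooled formula gives at 95% power. That is a separate matter and does not affect what follows.

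**2. Effect of adjustment on the interval.** If baseline variables explain a share R² of the outcome variance, the variance of the adjusted marginal estimate is about (1 − R²) times the unadjusted variance. The interval on the log scale then shrinks by the factor √(1 − R²), which is equivalent to n/(1 − R²) women.

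The documents give no R². The assumption is predictors with an AUC of about 0.58–0.68 for live birth, which implies an R² of about 1–9% in PIP-IVF (rates 17–30%), 1–6% in PIP-PCOS and 0.6–3.5% in PIP-UE.

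| R² | Interval narrower by | Extra women equivalent to 840/(1 − R²) − 840 |
|---|---|---|
| 1% | 0.5% | 8 |
| 5% | 2.5% | 44 |
| 9% | 4.6% | 83 |

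**3. Check of the approximation.** A simulation compared the standardised risk ratio from a logistic model with the unadjusted one (33% v 17%, 188 per arm, 1,500 runs).

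| AUC | R² | Variance of log RR, adjusted/unadjusted |
|---|---|---|
| 0.55 | 0.6% | 0.998 |
| 0.61 | 2.2% | 0.983 |
| 0.66 | 4.9% | 0.949 |
| 0.71 | 8.3% | 0.915 |

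The ratios follow 1 − R² closely.

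**4. Power at a smaller effect, PIP-IVF.** The Background quotes a review risk ratio of 1.42 for live birth. Applied to the 17% control rate this gives 0.17 × 1.42 = 24.1%, with 840/2 = 420 per arm. With m = n/(1 − R²) and mean rate 0.2055:

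z = [0.071√m − 1.96 √(2 × 0.2055 × 0.7945)] / √(0.17 × 0.83 + 0.241 × 0.759) = (0.071√m − 1.120)/0.5692

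- R² = 0: m = 420, z = 0.589, power 72.2% (72.6% at the unrounded 24.14%)
- R² = 1%: m = 424.2, z = 0.602, power 72.6%
- R² = 5%: m = 442.1, z = 0.655, power 74.4%
- R² = 9%: m = 461.5, z = 0.712, power 76.2%

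For the interval, the unadjusted SE of the log RR is √(0.83/71.4 + 0.759/101.2) = 0.138, which gives 1.08 to 1.86 around 1.42. At R² = 9% the SE is 0.132 and the interval 1.10 to 1.84.

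**5. Power at the stated design effects** (stated n per arm, before the contingency):

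| Trial | R² = 0 | 2% | 5% | 10% |
|---|---|---|---|---|
| PIP-IVF, 376 | 99.92% | 99.93% | 99.95% | 99.97% |
| PIP-IVF, 188 (one transfer type) | 95.1% | 95.4% | 96.0% | 96.8% |
| PIP-UE, 158 | 92.6% | 93.1% | 93.8% | 94.9% |
| PIP-PCOS, 126 | 91.7% | 92.2% | 93.0% | 94.2% |

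The largest gain is 94.2 − 91.7 = 2.5 points, and it needs an R² at or above the top of the assumed range.

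**The case against.** **An analysis plan that is not shown may list covariates.** This is fair: an article commonly leaves such detail to that plan, and the text never calls the risk ratio unadjusted. But the article does name regression and assigns it to subgroup effects, so the natural reading is a primary estimate without covariates. If an analysis plan already fixes an adjustment set, the sponsor need only confirm it. The baseline tests are stated outright, so no unseen document removes them.

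**The unadjusted risk ratio is valid.** This stands in full. A reader might infer that the planned estimate is biased, or that a chance age difference would bias it. The documents do not support that: chance imbalance is part of the sampling error that the interval already covers.

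**The predictors may be weak.** This also stands. A reader might call them strong, but no section gives the prognostic strength of any variable, and an AUC of 0.58–0.68 is modest prediction. The 9% end of the range belongs to a 30% live-birth rate. At the average rate of about 20.5% in step 4, an AUC of 0.68 explains about 7.3%, and power is then about 75%.

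**Baseline data have other uses.** A reader might infer that they feed significance tests only. That is wrong: previous failed transfers, duration of infertility and previous ovulatory cycles are subgroup factors for live birth. Nor does any section make adjustment depend on a baseline test. Post hoc adjustment is a possibility that a fixed list would close off, not something planned.

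**Conclusion.** The point holds as an efficiency improvement. As written, the live-birth risk ratio uses no baseline covariate, and baseline data are tested between arms to no inferential purpose.

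The gain from adjustment is real but modest. It is about 0.5–5% off the width of the interval, and 0.4 to 4 points of power in PIP-IVF at 17% v 24.1%. At the stated design effects it is at most about 2.5 points, and practically nothing for PIP-IVF as a whole. These figures rest on an assumed 1–9% of variance explained (10% as the upper limit in the design-effect table), which the documents neither give nor contradict. PIP-UE is likely to sit at the low end because its control live-birth rate is only 7%.

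No stated sample size is invalidated and no bias is corrected. The firmest part is the baseline testing, because it is a positive statement in the text and depends on no assumption.

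**What to change.** In the Statistical analysis section:

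1. Make the primary estimate a marginal risk ratio from a logistic model with standardisation, or from Poisson regression with robust standard errors.
2. Adjust for the randomisation strata (clinic in all trials; fresh or frozen-thaw transfer in PIP-IVF) and for female age as a continuous variable. Add previous failed transfers in PIP-IVF, duration of infertility in PIP-UE and previous ovulatory induction cycles in PIP-PCOS.
3. Fix this list before outcomes are compared, whatever the observed balance.
4. Use no drug variable in PIP-PCOS unless it is recorded before randomisation. The subgroup list defines the drug by what the woman was taking at conception, and the dose is collected through the study diary; both come after randomisation.
5. Keep the unadjusted risk ratio as a sensitivity analysis.
6. Replace the chi-squared and t-tests of baseline data with descriptive tables by arm.

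The cost is wording and slightly more modelling. No extra women are needed. The fertility-history variables and age are ones the plan already needs for its own analyses or eligibility checks. The article gives recruitment as ongoing and plans no interim analysis, so on its stated status the change could be made before any comparison of outcomes.

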### Randomisation

A third-party, Internet-based, data collection and randomisation system will be used to confirm participant eligibility and ensure allocation concealment; that is, participant allocations are concealed within the system until the patient is randomised. Only participants who meet the eligibility criteria can be randomised. In instances where computer or Internet access is not reliable, participants will be randomised using sequentially numbered, opaque, sealed envelopes. Dedicated PIP study personnel will be responsible for randomising participants at each site. Participants will be randomised in a 1:1 ratio using block randomisation of two different sizes between 5–15 repeating in random order, stratified by recruiting clinic and by fresh or frozen-thaw embryo transfer (the latter in PIP-IVF only).

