### Assessment of participant blinding

The sham procedure employed in PIP-UE and PIP-PCOS is designed to blind participants to their randomisation allocation. The sham procedure involves placing the pipelle in the posterior fornix and not inserting it through the cervix or into the womb, and hence it is expected to cause less pain on average than the interventional procedure. Although participants may not know how much pain to expect from either procedure, some participants may have prior expectations regarding the anticipated degree of pain from either procedure, and this may reduce the efficacy of the blinding. For example, women may have had previous intrauterine procedures or read information about endometrial biopsy on the Internet.

To assess whether participants in PIP-PCOS and PIP-UE are truly blinded to their study allocation, they will be asked to guess their study allocation (from the options of: pipelle procedure, placebo procedure or don’t know) and to supply a reason to support their guess. Participants will be randomised a second time following the procedure to either the ‘ask early’ group or the ‘ask late’ group. The ‘ask early’ group will be asked to guess their allocation within one week of the procedure, and the ‘ask late’ group will be asked to guess their allocation at the end of the study (that is, when the participant knows whether or not they have fallen pregnant in the study). Participants randomised to early will also be asked to guess again at the end of the study, to assess whether there are changes in response over time. Participants will be informed of their allocation after they guess their allocation at the end of the study.

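### The equal-variance methods named for pain (Student's t-test, ANOVA) can give wrong p values and intervals, in either direction, in the pain subgroup comparisons if subgroups differ in both size and spread

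*Protocol article*

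**What the plan says.** Pain during the procedure, on a 10 cm visual analogue scale, is a secondary outcome (Outcomes). The Statistical analysis section fixes the method: "For continuous outcomes (such as pain), the mean difference will be calculated and the student’s" t-test will be used. For subgroups, the same section says "ANOVA or logistic regression analysis will be used for the analysis of pre-specified subgroup effects". Of those two, only ANOVA fits a continuous outcome.

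The Subgroup analyses section states: "For the outcome of pain during the procedure the following subgroup analysis will be performed". It then lists three yes/no factors: previous cervical surgery, tenaculum use, and whether the procedure was done during menstruation. It names no method and gives no expected subgroup sizes. The list stands under the last PIP-UE heading, but its wording does not confine it to that study.

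Three other statements matter here:
- Randomisation: "Participants will be randomised in a 1:1 ratio".
- Table 1: in PIP-IVF, pain is recorded in the intervention group only.
- Assessment of participant blinding: the sham does not enter the cervix, "hence it is expected to cause less pain on average than the interventional procedure".

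**The concern.** Student's t-test and ordinary ANOVA estimate one variance from all groups together, and the larger group dominates that estimate. With groups of equal size this does no harm. With groups of unequal size, the standard error is too small when the smaller group has the larger spread, and too large when it has the smaller spread.

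Nothing in the design balances the pain subgroups. Pain is also bounded at zero, so a group with little pain has less room to vary than a group with more. Unequal size together with unequal spread is therefore plausible, though not documented.

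At stake are the results that would tell women and clinics who is likely to find the procedure painful. In PIP-IVF, subgroup contrasts are the only pain comparisons possible, because the control group has no pain score.

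**Working it through.** The article states no pain SD, pain effect or subgroup size, so there is no figure of its own to reproduce. The check asks how far Student's test departs from its nominal level.

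**Inputs from the article**
- Planned totals of 840, 350 and 280, randomised 1:1, give about 420, 175 and 140 women per arm.
- A two-sided 5% level is stated for the sample size and taken here as nominal for pain.

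**Assumptions**
- The smaller subgroup holds 10%, 20%, 30% or 50% of the women.
- Its SD is 0.67, 1, 1.25 or 1.5 times that of the larger subgroup, whose SD is set to 1.

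**Formulas**
- True variance of the mean difference: V = s1²/n1 + s2²/n2.
- Variance that Student's test uses, on average: P = [((n1−1)s1² + (n2−1)s2²)/(n1+n2−2)] × (1/n1 + 1/n2).
- True error: 2 × [1 − Φ(c × √(P/V))], with c the 97.5% point of t on n1+n2−2 degrees of freedom.

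**Randomised arms.** With n1 = n2 = n, P = ((s1² + s2²)/2) × (2/n) = (s1² + s2²)/n = V. The ratio is 1 whatever the SDs. For 140 or 175 per arm the formula gives 4.9% at every SD ratio from 1 to 3. Simulation at ratios 2 and 3 gives 5.0% to 5.4%. This comparison is unaffected.

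**One subgroup case in full.** Take 420 biopsies with 10% in the smaller subgroup (42 v 378) and SD ratio 1.5.
- V = 2.25/42 + 1/378 = 0.0562.
- Pooled variance = (41 × 2.25 + 377 × 1)/418 = 1.1226.
- P = 1.1226 × (1/42 + 1/378) = 0.0297.
- √(P/V) = 0.727, so Student's interval is about 27% too narrow.
- c = 1.966, and 1.966 × 0.727 = 1.429, which gives a true error of 15.3%.

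**Range, 420 women: true error of Student's test at nominal 5%**

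| Smaller subgroup | SD ratio 0.67 | 1 | 1.25 | 1.5 |
|---|---|---|---|---|
| 10% (42 v 378) | 0.7% | 4.9% | 10.0% | 15.3% |
| 20% (84 v 336) | 1.3% | 4.9% | 8.5% | 12.1% |
| 30% (126 v 294) | 2.2% | 4.9% | 7.2% | 9.3% |
| 50% (210 v 210) | 4.9% | 4.9% | 4.9% | 4.9% |

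Totals of 140 and 175 give nearly the same values, so little depends on which study the subgroup list covers. Normal simulations agree with the formula. Welch's test stayed at about 4.5% to 5.5% in every case simulated.

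**Bounded scale with a true difference.** Scores were drawn from beta distributions on 0 to 10, with 42 v 378 women and assumed means and SDs.
- Means 4 v 3, SDs 2.5 v 2.0: Student's 95% interval covers the true difference about 90% of the time, Welch's about 95%.
- Means 4.5 v 2.5, SDs 2.5 v 1.67: about 85% against about 95%.

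**The case against.** The strongest reply is that the two premises are not in the article. It gives no subgroup size and no pain SD. The blinding section speaks only of average pain between sham and biopsy, which says nothing about spread within the pain subgroups. Both conditions must hold together, and if either fails the error is about 5%. This stands, and the point is therefore conditional.

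A second reply is that the reason offered for unequal spread, scores clustering near zero, works through a difference in mean pain, and where means truly differ a significant result is not a false positive. That is fair for the type I error figures. It does not rescue the intervals, as the bounded-scale check shows.

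A third reply is that the choice between Student's and Welch's test belongs in the statistical analysis plan. That would hold had the article left the test open, but it names Student's. It is true that the subgroup list names no method, so applying ANOVA there is an inference from the Statistical analysis section. No other suitable method is stated.

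A reader might infer two stronger things, and the article supports neither:
- That pain differences will be declared too often. If the smaller subgroup has the smaller spread, Student's test is conservative instead, and nothing in the article settles the direction.
- That less variable sham scores will shrink error bars within the biopsy arm. No section says that the arms will be pooled in one ANOVA.

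**Conclusion.** The point holds in conditional form and is minor. The article names equal-variance methods for pain and plans pain subgroups that nothing in the design balances. If subgroups differ in both size and spread, p values and intervals will be wrong. Under the assumed 10% to 30% minority share and SD ratios of 0.67 to 1.5, the true error of a nominal 5% test runs from under 1% to about 15%. The shares and ratios are assumptions, and the direction is unknown.

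The randomised biopsy versus sham comparison of pain is sound as planned. Live birth, the sample sizes and the main conclusions are untouched.

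**What to change.** In the Statistical analysis section, name Welch's (unequal-variance) t-test for pain in place of Student's. State that any ANOVA or regression of pain by subgroup will use heteroscedasticity-robust standard errors.

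The cost is a change of wording. It needs no extra data or participants, and in the simulations it lost nothing on type I error when variances were equal. It also removes the need to guess which subgroup has the larger spread, because Welch's test corrects the error in both directions.
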